### Intervention

#### Training of occupational physicians in the intervention group

OPs receive a two-day training in the SHARP-at work intervention. Training is provided by experienced trainers in occupational health interventions.

#### Treatment of participants in the intervention group

The intervention consists of five steps the employee has to undertake when return-to-work is started. The OP monitors that the employee follows these steps and uses interventions to activate the employee when needed. The five steps are delineated below.

1. Make an inventory of problems and/or opportunities encountered at work

2. Brainstorm on solutions

3. Write down the solutions and the support needed and assess the applicability

4. Discuss the solutions with the line manager and make an action plan

5. Evaluate the action plan and the implementation of solutions

The OP can use assignments for the employee to write down and structure the process. In general, the OP will counsel on the process level. (S)he does not discuss the content of problems and solutions but challenges the employee to reflect on the relative seriousness of problems and the feasibility of solutions. This can be done by asking questions that stimulate the employee to think about possible perspectives. This form of guidance is related to Socratic questioning. The intervention differs from the guideline of the Netherlands Society of Occupational Medicine by the emphasis on problems and possibilities encountered *at work *when an employee has already returned to work.

### Care as usual

#### Training of occupational physicians in the control group

All OPs participating in the study are trained in the guideline of the Netherlands Society of Occupational Medicine. There is no additional training of OPs in the control group as part of this study. At the end of the study period these OPs will be trained in the SHARP-at work intervention if it proves to be effective.

#### Treatment of participants in the control group

CAU is delivered according to the evidence-based guideline of the Netherlands Society of Occupational Medicine [21,22]. CAU comprises guidance in regaining control and activating problem solving when the employee is still on sickness absence and at least one consultation session after return-to-work, addressing relapse prevention.

### Sample size

For the power calculation, recurrent sickness absence days are considered the primary outcome measure. To calculate the sample size, administrative data from the sickness absence registry of the OHS was used. From 2001 to 2007, recurrent sickness absence days among employees, who had returned to work after a period of sickness absence because of CMDs, were registered. For the power calculation, only recurrent sickness absence days of the first recurrence episode until 1 year later were used to approximate the 1 year follow-up of the present study (N = 4443). The variance in recurrent sickness absence days at the level of the OP was taken into account.

During the above-mentioned period, the mean days of recurrent sickness absence was 68.5 (standard deviation is 119.6). The target of the present study is to reduce the recurrent sickness absence days with 20%, i.e. an average of 12.7 recurrent sickness absence days per employee per year. The OPs in this OHS's dataset were randomly divided into two groups. One group was called "the intervention group" from which 20% of the recurrent sickness absence days was subtracted to create the difference between the intervention and control group and to calculate an effect size.

For a decrease of 12.7 recurrent sickness absence days per employee during 1 year at alpha = 0.05 and ICC = 0.05, 50 OPs, each providing five employees, need to be included in each group (the intervention and control group) [29]. The five employees must be viewed as the average number per OP. For this multilevel power calculation, an effect size of 0.18 was taken into account. This effect size was calculated by using a logtransformation on the data to create a normal distribution and subsequently by dividing the difference in mean days of recurrent sickness absence between the intervention and control group (difference is 0.25) by the standard deviation (standard deviation of difference is 1.4). To include the effect size in the multilevel power calculation, it had to be transformed to a correlation coefficient, which resulted in a correlation of 0.09 [30].

The collaborating OHS serves approximately one million insured employees. A total of 350 OPs is working for this OHS and each OP serves around 2500 to 3000 employees. Of these employees it is estimated that 1.3% (30% of the national sickness absence rate among Dutch employees of 4.3%) will be on sickness absence because of a CMD during a 1 year period [31]. Therefore, an OP will see around 32 to 39 employees per year who are absent because of CMDs. Following this, the source population of the OHS is large enough to recruit the required number of OPs and employees according to the sample size calculation.

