## Background

Common mental disorders (CMDs), such as depression, anxiety disorder, and adjustment disorder, have emerged as a major public and occupational health problem in many countries [1]. Several studies have found a relationship between CMDs and long term sickness absence and work disability [2-7]. In the Netherlands, about one in every three new work disability benefit recipients is disabled for work because of mental health problems [8,9]. The increase in sickness absence and work disability because of CMDs has serious negative economical consequences calling for preventive action [3,5,7,10,11].

Recently, attention is also given to the at-work decrements in performance because of CMDs, which seems to be even more costly than absenteeism [1,6,12-15]. In their review, Lerner and Henke show that depression is significantly associated with a reduction of job performance and productivity; it was demonstrated that employees with a significant improvement in depression still have more trouble with performing well compared to their healthy colleagues [6]. These findings emphasize the importance of interventions aiming at employees with CMDs who are at work. Yet, most interventions for employees with mental health problems are curative and focus on reintegration [16-20]. No interventions exist which aim at providing support after return-to-work although it is known that employees who return to work often are not fully recovered from their initial complaints [18-20]. Moreover, research in the Netherlands showed that one out of five employees who have returned to work after a sickness absence period because of a CMD experiences a relapse of sickness absence due to CMDs (Koopmans et al., submitted for publication). For these reasons, we have developed an intervention aiming at the prevention of a relapse of sickness absence among employees who have (partially/fully) returned to work after a period of sickness absence because of a CMD.

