### Recruitment of participants

#### Inclusion criteria

Employees participating in the study are between 18 and 63 years old and employed in a paid job. Furthermore, they have: 1. a diagnosis of a CMD given by their OP at the start of the sickness absence period, 2. a period of sickness absence due to a CMD of at least two weeks, and 3. a planned return-to-work within two weeks.

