### Primary outcome

The primary outcome measure is a relapse of sickness absence, measured as cumulative recurrent sickness absence days. A relapse is defined as a 30% decrease in working days per week or a decrease of at least one day per week because of sickness absence. Recurrent sickness absence days are operationalised as days of sickness absence among employees who have worked a steady amount of days during the first two weeks after they have returned to work. This information will be obtained by record linkages with the sickness absence registry of the OHS and by the employee questionnaires.

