#### Effect evaluation

The primary outcome variable "cumulative recurrent sickness absence days during follow-up" will be compared between the intervention and control group in the multilevel regression analyses. Time until a relapse of sickness absence will be examined by using Cox proportional hazard analysis to estimate hazard ratio's for a relapse and the 95% confidence interval. In case no software is available to conduct these analyses in a multilevel structure, cluster level survival analyses will be conducted with means for each cluster. In these analyses, cluster size will be introduced as a weighting factor. To investigate differences between the intervention and control group in changes (improvement) on all secondary outcomes, multilevel longitudinal analysis will be used. Pre-planned subgroup analyses on type of CMD, line manager participation in the study, size of the company, perceived decision latitude, type of work, and expectancy to stay-at-work will be conducted.

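### The planning values come from recurrence episodes and appear to hold no zeros, so 12.7 days and d = 0.18 do not describe a 20% reduction per enrolled returner

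*Protocol article*

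**What the plan says.** The Sample size section plans on occupational health service (OHS) registry data from 2001 to 2007 (N = 4443) and says that "only recurrent sickness absence days of the first recurrence episode until 1 year later were used to approximate the 1 year follow-up". It reports a mean of 68.5 days and an SD of 119.6. It sets a 20% reduction as the target and expresses this as 12.7 days for each employee and year. The effect size of 0.18 was obtained "by using a logtransformation on the data to create a normal distribution", as a log-scale difference of 0.25 over an SD of 1.4. With alpha 0.05, an ICC of 0.05 and five employees per occupational physician (OP), the section asks for 50 OPs, hence 250 employees, in each group. It does not state the power.

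The trial population is wider. Under Inclusion criteria an employee needs, among other things, "a planned return-to-work within two weeks"; a recurrence is not an entry condition. Under Primary outcome, "The primary outcome measure is a relapse of sickness absence, measured as cumulative recurrent sickness absence days", and the days that count are "days of sickness absence among employees who have worked a steady amount of days during the first two weeks after they have returned to work". Statistical analyses applies intention to treat, and Effect evaluation says the cumulative days "will be compared between the intervention and control group in the multilevel regression analyses". The Background reports that "one out of five employees who have returned to work after a sickness absence period because of a CMD experiences a relapse".

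**The concern.** An employee who never relapses has no first recurrence episode. Such employees therefore seem to be absent from the planning data, although they enter the primary analysis with zero days. A mean and SD taken per recurrence would then have been carried over to a target stated per employee. If so, 12.7 days is a much larger share of the real per-employee burden than the intended 20%, and 0.18 is not the standardised effect on the primary outcome. A null result could then be read as evidence against the intervention from a trial that was never sized for its own outcome.

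**Working it through.** **The plan's own figures**

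- Effect size: 0.25 / 1.4 = 0.179, stated as 0.18. Correlation: 0.18 / sqrt(0.18² + 4) = 0.090, stated as 0.09. Both reproduce.
- Design effect: 1 + (5 − 1) × 0.05 = 1.2. Standard error of d with 250 per group: sqrt(2 × 1.2 / 250) = 0.098.
- Power at d = 0.18, two-sided 0.05: Φ(0.18 / 0.098 − 1.96) = 45%. One-sided it is 58% (the article does not state sidedness). So 250 per group does not reproduce at a conventional power.
- 20% of 68.5 is 13.7, not 12.7. This is a separate discrepancy; 12.7 is kept below as the stated target.

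**Do the planning data contain zeros?** The article does not say so outright. Three checks:

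1. *SD bound.* If 68.5 were the mean over all returners and a share p had any days, the SD would be at least 68.5 × sqrt((1 − p) / p). At p = 0.20 this is 137, above the stated 119.6. The stated mean and SD require p ≥ 68.5² / (68.5² + 119.6²) = 24.7%, and that minimum needs all episodes to be equally long.
2. *Log difference.* The article took 20% of the days away from a random half of the OPs. With every value positive this shifts the log mean by |ln 0.8| = 0.223, close to the reported 0.25. Simulating log(x + 1) with 20% non-zero gives about 0.04, and with 50% non-zero about 0.10. The chance error of the split, ignoring clustering, is about 1.4 × 2 / sqrt(4443) = 0.042. So 0.25 is within one standard error of the no-zeros value and several away from the others. The log SD of 1.4 does not discriminate: the simulation gives about 1.5 at 20% non-zero as well.
3. *Transformation.* A log transformation cannot bring data with a large mass at zero to normality.

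All three point to planning data with essentially no zeros.

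**All enrolled returners.** Assume a share p has recurrent days with mean 68.5 and SD 119.6, and the rest have zero.

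- Mean = 68.5p; SD = sqrt(p × (119.6² + 68.5²) − mean²)
- d = 0.2 × mean / SD; power = Φ(d / 0.098 − 1.96)

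For p = 0.20: mean 13.7; SD = sqrt(0.2 × 18996.4 − 187.7) = 60.1; d = 2.74 / 60.1 = 0.046; power Φ(0.465 − 1.96) = 7%.

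| Assumed p | Mean (days) | SD | 20% reduction (days) | 12.7 as share of mean | d | Power |
|---|---|---|---|---|---|---|
| 0.20 | 13.7 | 60.1 | 2.7 | 93% | 0.046 | 7% |
| 0.30 | 20.6 | 72.6 | 4.1 | 62% | 0.057 | 8% |
| 0.40 | 27.4 | 82.8 | 5.5 | 46% | 0.066 | 10% |
| 0.50 | 34.3 | 91.2 | 6.9 | 37% | 0.075 | 12% |

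One-sided power runs from 12% to 19% over the same range. The mean of 13.7 in the first row equals 20% of 68.5 only because the share and the reduction are both 20%.

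**How much of the shortfall is due to zeros?** Power is 45% at the protocol's own d = 0.18. On raw days among recurrers only, d = 12.7 / 119.6 = 0.106 and power is Φ(0.106 / 0.098 − 1.96) = 19%. Adding the zeros takes it from 19% to 7–12%.

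**The case against.** Several points on the other side are sound.

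- *The zero share is not known.* A reader might infer from the Background that four in five enrolled employees will have zero days. That figure covers relapse due to CMDs only and has no time window, and the Primary outcome section does not restrict recurrent absence to CMD causes. The zero share may be well below 80%. For the same reason the SD bound does not prove that the two figures cannot describe one population: it excludes 20% non-zero, but not every share above 24.7%.
- *The 7% is not all due to zeros.* A reader might charge the whole loss to the population mismatch. Most of the gap to a conventional 80% is already there at the protocol's own effect size and on the raw day scale.
- *The day-scale test is an assumption.* Effect evaluation names only multilevel regression. If the 20% acted on the proportion relapsing instead, power would be about 18% for 20% falling to 16%, and about 54% for 50% falling to 40%.
- *No log-normal analysis is planned.* A reader might infer that the primary model cannot be run on zeros. The log transformation appears only in the derivation of the effect size, and the added Cox analysis accommodates employees who do not relapse.
- *The article says the data approximate the follow-up.* That wording addresses the one-year window and does not cover the missing non-recurrers.

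These points limit the size and certainty of the finding. None of them makes 12.7 days a 20% reduction per enrolled employee.

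**Conclusion.** The point holds in a limited form. The mean, SD and effect size appear to be values per recurrence, whereas the primary outcome is cumulative days in all enrolled returners. As written, the 12.7-day target and d = 0.18 do not describe a 20% reduction per enrolled employee. Across assumed recurrence shares of 20% to 50%, 12.7 days is 93% to 37% of the expected mean, and a day-scale comparison has about 7% to 12% power.

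These figures rest on recurrers having mean 68.5 and SD 119.6, on the reduction applying to the all-returner mean, and on a two-sided comparison of means. Counting later episodes could raise the recurrers' days, and a recurrence late in follow-up would be cut off at 12 months; the article quantifies neither. The documents do not support a fixed zero share of 80%, the claim that the zeros alone cause the low power, or the claim that the planned analysis is unworkable.

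**What to change.** 1. In the Sample size section, say whether employees without a recurrence are among the 4443.
2. From the OHS registry, take all employees who returned after CMD absence, with zeros and all episodes included, for 12 months from return-to-work. If this cannot be obtained, work over a stated range of recurrence shares.
3. From those data, restate the mean, the SD, the 20% target in days per enrolled employee, and the power that 500 employees give.
4. State that the primary analysis must be valid for days with many zeros in all returners, and that the power calculation must match that analysis. The choice of model can be left to the SAP; a two-part or negative-binomial model is one option among several and need not be imposed here.

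Cost: one further registry extract, because data limited to recurrers cannot supply the zeros; a rewritten paragraph in the Sample size section and a sentence in the analysis section; and a less favourable stated power.

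### The planned 20% reduction appears as 18.5% in days (12.7 of 68.5) and about 22% on the log scale (0.25), so d = 0.18 is larger than the stated target supports

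*Protocol article*

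**What the plan says.** All the figures are in the Sample size section of the protocol article.

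- **Registry data.** For 2001 to 2007 "the mean days of recurrent sickness absence was 68.5 (standard deviation is 119.6". The power calculation is said to use only days of the first recurrence episode up to one year (N = 4443).
- **Target.** The aim is to "reduce the recurrent sickness absence days with 20%, i.e. an average of 12.7 recurrent sickness absence days per employee per year". The figure of 12.7 days is repeated as the decrease for which the sample size is given.
- **How the effect was built.** "The OPs in this OHS's dataset were randomly divided into two groups". One was labelled the intervention group, "from which 20% of the recurrent sickness absence days was subtracted to create the difference between the intervention and control group".
- **Effect size.** After a log transformation, it is the difference in means "between the intervention and control group (difference is 0.25) by the standard deviation (standard deviation of difference is 1.4". The section continues: "For this multilevel power calculation, an effect size of 0.18 was taken into account". For the multilevel calculation "it had to be transformed to a correlation coefficient, which resulted in a correlation of 0.09".
- **Design.** Alpha is 0.05, ICC is 0.05, and each group has 50 OPs with an average of five employees. Neither power nor sidedness is stated.

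**The concern.** One target, a 20% reduction, appears in two forms, and neither equals 20%. In days it falls short of 20% of the printed mean; on the log scale it exceeds it. Because the discrepancies run in opposite directions, a reader cannot tell which effect the trial is planned to detect.

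The log-scale figure matters more, because it sets d = 0.18 and r = 0.09, the inputs to the sample size. The method behind it is also weak. A difference between two random halves, one of them cut by 20%, equals the intended effect plus whatever difference the halves had before the cut. A planning effect should not depend on one random draw when the pooled data give it directly.

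**Working it through.** **Inputs (all from Sample size):** mean 68.5 days, SD 119.6 days, reduction 20% given as 12.7 days, log difference 0.25, log SD 1.4, N = 4443, alpha 0.05, ICC 0.05, 50 OPs × 5 = 250 employees per group.

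**1. The protocol's own chain.** d = 0.25 / 1.4 = 0.179, which rounds to 0.18. r = d / √(d² + 4) = 0.18 / √(0.0324 + 4) = 0.0896, which rounds to 0.09. Both reproduce, so the question lies in the 0.25.

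**2. Day scale.** 0.20 × 68.5 = 13.7. Conversely, 12.7 / 68.5 = 0.185 and 12.7 / 0.20 = 63.5. A whole day is too much for rounding, and 63.5 is not printed anywhere.

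**3. Log scale.** Multiplying every value by 0.8 shifts each natural log by ln(0.8) = −0.223. The printed 0.25 means a cut of 1 − exp(−0.25) = 22.1%; over its rounding range (0.245 to 0.255) the cut is 21.7% to 22.5%. Other conventions do not help. Base 10 gives 0.097. Log(x+1) gives less than 0.223, about 0.205 under an assumed lognormal distribution.

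**4. Effect size for a 20% cut.** d = 0.223 / 1.4 = 0.159. Allowing for the rounding of 1.4 (1.35 to 1.45), d lies between 0.154 and 0.165. r = 0.159 / √(0.159² + 4) = 0.079. The protocol's 0.18 is outside this range.

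**5. Could the random split account for the gaps?** Ignoring clustering, the standard error of the difference between two halves of 4443 is SD × √(4/4443):

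- Log scale: 1.4 × 0.0300 = 0.042.
- Day scale: 119.6 × 0.0300 = 3.6 days.

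With ICC 0.05 and an assumed 100 to 350 OPs in the registry, these become 0.053 to 0.075 and 4.5 to 6.4 days. The gaps to explain are 0.25 − 0.223 = 0.027 and 13.7 − 12.7 = 1.0 day, each below one standard error. In a simulation of the procedure (lognormal days, 200 OPs and ICC 0.05 assumed), a difference of at least 0.245 arose in about 37% of runs.

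**6. Consequence for power.** The design effect is 1 + (5 − 1) × 0.05 = 1.2. The standard error of d is √(2 × 1.2 / 250) = 0.098. Power is Φ(d / 0.098 − 1.96), taking alpha as two-sided, which is an assumption.

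| d | Two-sided power, 250 per group |
|---|---|
| 0.18 | 45.1% |
| 0.159 | 36.9% |

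If alpha were one-sided, the figures would be 57.6% and 49.3%.

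**The case against.** The strongest objection concerns the 0.25. A reader might infer that a 20% cut cannot yield it, so that the figure is an arithmetic error. The document does not support that. It defines 0.25 as the difference between two random groups after one was cut, and an imbalance of 0.027 is well within chance. This stands: the procedure can produce 0.25. It does not rescue the figure as a planning effect, because the excess over 0.223 would then be noise counted as treatment effect.

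Nor can chance imbalance be called the established cause, since the half means are not reported. One split does not obviously explain both figures:

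- If 12.7 is the difference between equal halves averaging 68.5, then c + i = 137 and c − 0.8i = 12.7. Before the cut this gives about 69.1 for the intervention half and 67.9 for the control half. The control half is then lower in days, while the log excess needs it higher. Skewed data allow this, but it is not a natural shared explanation.
- If 12.7 is 20% of an intervention-half mean of 63.5, the control half averages 73.5. That gap of 10 days compares with a standard error of 3.6 to 6.4.

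A slip or a different base remains possible. It is unclear whether 68.5 describes the restricted first-episode, one-year data or a wider set, so the text does not show which of 68.5, 20% and 12.7 is wrong. Likewise, 0.223 assumes natural logs and a proportional cut to every record, which the section does not spell out.

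Finally, the practical effect is modest. One day is small against an SD of 119.6, and d moves only from 0.18 to 0.16.

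**Conclusion.** The inconsistency stands. As printed, 12.7 days is not 20% of 68.5, and 0.25 exceeds what a proportional 20% cut gives on the natural-log scale. For the stated target, d is 0.16 (0.154 to 0.165) and r is 0.08. The random split is a plausible but unconfirmed source of the excess.

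The cost is about eight percentage points of power, from roughly 45% to 37%, under an assumed two-sided test and the protocol's ICC of 0.05. A reader might infer that this discrepancy is why the trial looks underpowered. It is not: most of the gap to a conventional level already exists at the protocol's own d = 0.18, and that is a separate issue. Nor has it been shown that this input alone fixed the number of OPs, since no power target is stated. This is a planning figure that should be corrected, at low cost.

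**What to change.** In the Sample size section:

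1. Reconcile 68.5, 20% and 12.7, and say which data the mean describes. If 68.5 is the base, the target is 13.7 days; if the base is 63.5, print that mean.
2. Derive the log effect directly from the pooled data as ln(0.8) = −0.223, giving d = 0.16 and r = 0.08, and state the transformation used. Drop the single random split. If 0.25 is kept, report the means of both halves before the cut and explain the excess.
3. State the sidedness and the power that 50 OPs with five employees each per group provide at the corrected effect: about 37% if two-sided.

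The cost is a few corrected figures in one section and a less favourable planning statement. This point asks for no extra enrolment.

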Given the serious consequences of CMDs for the individual employee and the high social and economic costs for the workplace, the employer, the health system, and society, the promotion of sustainable work participation among employees with CMDs is very important. Therefore, the primary aim of this study is to evaluate the effectiveness of the SHARP-at work intervention compared to care as usual (CAU) in preventing a relapse of sickness absence among employees who have returned to work after a period of sickness absence because of a CMD. We hypothesise that employees who return to work, after sickness absence because of a CMD, and undergo the SHARP-at work intervention will have less recurrent sickness absence days compared to employees who receive CAU. Secondary aims are to improve mental health and work functioning and to stimulate better coping mechanisms. In addition, the cost-benefit of the intervention will be examined. Along with these evaluations, we will conduct a process evaluation among employees, OPs, and line managers. Finally, prognostic factors for a relapse of sickness absence will be investigated. To our knowledge, this is the first study focussing on guiding employees at work after they have returned to work because of a period of sickness absence due to CMDs.

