A limitation of the study is the inclusion of participants by the OPs. The possibility exists that OPs in both study groups select those employees who have, in their view, good potential for fast recovery and small chances for a relapse of sickness absence. Although it has been stressed to all OPs to invite all employees eligible for the study, we can not exclude the possibility of bias. Questions to investigate if participating employees were thought to be more suitable for the study are included in the process evaluation for OPs. Another possibility for bias to occur is the selection of employees who have a good relationship with their OP. Unfortunately, we can not exclude this bias, but we ask questions in the process evaluation on the relationship between the OP and the employee. Finally, recruiting 500 employees for the study is a challenge. Most studies in this field have problems with recruiting participants. We have tried to minimise these problems by embedding this study in one large OHS. All participating OPs work for the same OHS and are stimulated to contribute to the study by this OHS. Moreover, we expect fewer refusals to participate because OPs invite employees to participate in the study. The OP has already built a relationship with the employee which will contribute to a safe environment to make the choice to participate in the study.

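### The stated 50 OPs × 5 employees per arm give about 45% power two-sided (58% one-sided) on the paragraph's own inputs, so the number presented as needed does not follow from them

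*Protocol article*

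**What the plan says.** The Sample size section bases the calculation on recurrent sickness absence days, the primary outcome. It fixes the error rate and the clustering, "at alpha = 0.05 and ICC = 0.05", and concludes that "50 OPs, each providing five employees, need to be included in each group (the intervention and control group". It adds that "The five employees must be viewed as the average number per OP".

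On the effect it says: "For this multilevel power calculation, an effect size of 0.18 was taken into account". That value comes from log-transformed registry data, as a ratio whose two parts are given as "difference is 0.25) by the standard deviation (standard deviation of difference is 1.4". It was then converted to a correlation, "which resulted in a correlation of 0.09".

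Under Methodological considerations the total is confirmed: "recruiting 500 employees for the study is a challenge".

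The article states neither a target power nor whether the test is one- or two-sided. The hypothesis in the Background is directional: employees in the intervention group "will have less recurrent sickness absence days compared to employees who receive CAU".

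**The concern.** A statement that a given number of clusters and employees is needed for a given effect implies that this number gives a reasonable chance of detecting it. Here the expected z at the targeted effect (1.84) is below the two-sided critical value (1.96). The printed number therefore cannot be the answer to a conventional calculation with the printed inputs.

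This is the central justification of the design, for the primary outcome. A reader told that 500 employees are what a 20% reduction requires would tend to take a non-significant result as evidence that no such reduction exists. On the printed inputs that inference would be unsafe. The Care as usual section also makes later training of the control OPs depend on the intervention proving effective, so a missed effect would have a practical consequence.

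**Working it through.** **Inputs, all from the Sample size section:** alpha 0.05; ICC 0.05; m = 5 employees per OP; 50 OPs per arm, so n = 250 per arm and 500 in total; d = 0.18; r = 0.09. No dropout allowance is stated, and none is assumed here.

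**The printed effect sizes agree with each other.** 0.25/1.4 = 0.179, which rounds to 0.18. With two equal groups r is close to d/2 = 0.09.

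**Power of 50 × 5 per arm**

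- Design effect: 1 + (5 − 1) × 0.05 = 1.2
- Standard error of d: sqrt(2 × 1.2/250) = 0.0980
- Expected z: 0.18/0.0980 = 1.837
- Two-sided power: Φ(1.837 − 1.960) = 0.451
- One-sided power: Φ(1.837 − 1.645) = 0.576
- Correlation form: 0.09/sqrt(1.2/500) = 1.837, the same z

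**Other readings of the paragraph**

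| Reading | Two-sided | One-sided |
|---|---|---|
| d = 0.18, ICC 0.05 | 45% | 58% |
| Same, t-test with 98 df | 44% | 57% |
| d = 0.18, clustering ignored (ICC 0) | 52% | 64% |
| d = 0.25, with 1.4 taken as the SD of a difference | 73% | 82% |
| Untransformed days, 12.7/119.6 = 0.106 | 19% | 29% |

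The d = 0.25 row uses a per-person SD of 1.4/sqrt(2) = 0.99, so d = 0.25/0.99 ≈ 0.25. That contradicts the printed 0.18 and r = 0.09. Among the readings that keep 0.18, the highest power is 64%.

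Five per OP is only an average. If cluster sizes vary with a coefficient of variation between 0.3 and 0.8 (an assumption; the article gives no figure), the design effect 1 + ((1 + CV²) × 5 − 1) × 0.05 runs from 1.22 to 1.36. Two-sided power then falls from about 44% to 41%.

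**Size needed for 80% power at d = 0.18**

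- Two-sided: 2 × (1.960 + 0.842)²/0.18² × 1.2 = 581.4, so 582 employees per arm; 582/5 rounds up to 117 OPs
- One-sided, by the same formula with 1.645: 459 employees, 92 OPs per arm

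**Effect detectable with 250 per arm at 80% power, two-sided**

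- d = 2.802 × 0.0980 = 0.274
- Log difference: 0.274 × 1.4 = 0.384
- If natural logs were used: 1 − exp(−0.384) = 32% reduction
- The stated log difference on the same scale: 1 − exp(−0.25) = 22% reduction

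**A separate mismatch in the same paragraph.** 20% of 68.5 is 13.7 days. The printed 12.7 is 12.7/68.5 = 18.5% of that mean, or 20% of 63.5. This does not alter the power figures based on d = 0.18.

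**The case against.** The strongest objection is that no stated power is contradicted. The article gives no target, and a full protocol or analysis plan that is not shown may give one. The shortfall is measured against the conventional 80%. That is correct, and it limits the point: a reader might infer that the trial claims 80% power and misses it, but the article makes no such claim. Nor does it describe the trial as adequately powered; the remark on the size of the source population concerns recruitment only. What remains is that presenting a number as needed implies some target, and 45% to 58% is hard to defend as one.

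A second objection is sidedness. A reader might infer that the trial is more likely to miss the target effect than to find it. That holds for a two-sided test. Sidedness is not stated and the hypothesis is directional; with a one-sided test power is 58%, and the statement would be false.

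Third, the fault may lie in the reported effect size and not in the number of employees. Taken literally, the SD of 1.4 belongs to a difference, and that reading gives 73% two-sided or 82% one-sided. It does not rescue the paragraph, because it conflicts with the printed 0.18 and 0.09. It is a reason to reconcile the inputs before any new figure is printed.

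Covariate adjustment is a weaker defence. To reach 80% two-sided it would have to explain about 1 − 250/582 = 57% of the outcome variance, and the article assumes nothing of the kind.

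**Conclusion.** The point holds: the stated number of OPs and employees does not follow from the stated inputs at any conventional power. With d = 0.18, alpha 0.05, ICC 0.05 and five employees per OP, power is about 45% two-sided or 58% one-sided, and 80% two-sided power would take about 2.3 times the planned employees (582/250).

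The figures assume a normal approximation, equal cluster sizes and no dropout. Unequal clusters or dropout would lower them.

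A reader might also set the detectable 32% against the targeted 20%. That mixes scales. The comparison on one scale is 32% against the 22% implied by the stated log difference of 0.25, and both percentages depend on natural logs, which the article does not specify.

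**What to change.** Keep the 500 employees and correct the paragraph in this order:

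1. State whether the primary test is one- or two-sided.
2. Reconcile the inputs: say whether 1.4 is the SD of the log outcome or of a difference, which logarithm was used, and whether the target is 13.7 days (20% of 68.5) or 12.7 days, and of which mean.
3. Recompute from the reconciled inputs, and replace the claim that this size is needed with the power it gives. If the printed inputs stand, that is about 45% two-sided (58% one-sided) for d = 0.18, with an effect detectable at 80% power of about 0.27 SD two-sided. That is a log difference of about 0.38, or roughly a 32% reduction under natural logs, against about 22% for the stated 0.25.
4. Add that a non-significant primary result will be read through its confidence interval and not as evidence against the targeted reduction.

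The cost is a rewritten paragraph and, on the printed inputs, a less favourable power statement. No extra OPs or employees are required.
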